## Abstract

**Background:**

Coronary artery stenosis is the major pathological change of coronary heart disease (CHD). Within the framework of traditional Chinese medicine (TCM) theory, some kinds of TCM Zheng could exist in patients with CHD; accordingly, TCM practitioners could provide appropriate TCM therapy. However, little is known about the association between TCM Zheng and types of coronary artery stenosis. Such knowledge could help improve the accuracy and effectiveness of efforts to combine CHD treatment with TCM therapy. Therefore, the aim of this study is to determine the association between TCM Zheng and types of coronary artery stenosis.

**Methods and Design:**

This is a multicenter, large sample, case series study in 4 tertiary A hospitals from 3 provinces in China. A total of 3,000 eligible patients diagnosed with atherosclerosis or CHD and selected to undergo coronary angiography (CAG) will be enrolled in this study. We will use electronic case report forms (eCRF) to collect information, including baseline characteristics, TCM symptoms, CAG results, and GRACE scores according to standard operating procedures (SOP). Data will be analyzed by SPSS 20.0.

**Ethics:**

This study is approved by the Ethics Committee of Guang'anmen Hospital of the China Academy of Chinese Medical Sciences (no. 2017-058-KY-01) and is registered with chictr.org (registration number ChiCTR-ROC-17013221).

## 1. Introduction

Coronary heart disease (CHD) is currently the leading cause of death worldwide. According to an analysis of the causes of death and disease burden in the global population over the past 20 years, the number of deaths caused by CHD worldwide was 7,029,300 in 2010, accounting for 13% of total deaths [1]. According to the 2016 report on cardiovascular disease in China, the number of deaths from CHD was 11 million in 2015, the death rate of CHD in urban residents was 110.67/100 thousand, and the mortality rate of rural residents was 110.91/100 thousand in 2015. In addition, the total cost of hospitalization due to acute myocardial infarction represented an average annual growth of 30.13% since 2004 [2]. Increasing burden of CHD has become a major public health problem; thus, improvements in the prevention and treatment of CHD are urgently needed.

Traditional Chinese medicine (TCM) has always been an essential part of the health care service system in China. It is well known that TCM practitioners usually prescribe herbal formulas or provide other TCM therapies based on Zheng differentiation of every patient using four diagnostic methods, including inspection, listening and smelling, inquiry, and palpation of the pulses. For CHD, a high-quality systematic review [3] concluded that treating CHD with some of the herbs used in TCM might be effective in alleviating angina symptoms, myocardial perfusion abnormalities, or neurological deficit. Furthermore, TCM might have the potential benefit of reducing major adverse cardiac events [4]. In addition, a large number of studies pertaining to the mechanism of herbal medications have shown that the herbs used to treat CHD address such functions as dilating blood vessels, improving microcirculation, reducing blood viscosity, regulating blood lipids, and enhancing energy metabolism and anti-inflammation [5].

However, it is worth mentioning that if TCM doctors had a comprehensive understanding of the difference in Zheng distribution of different types of CHD and stratifications of the Global Registry of Acute Coronary Events (GRACE) score, there might be less therapeutic error, and treatments might be more target-specific. Based on the degree of stenosis and treatment options, coronary stenosis can be divided into 5 types, including atherosclerosis with less than 30% stenosis, borderline coronary lesion with 30% to 70% stenosis, scheduled to undergo percutaneous coronary intervention (PCI), scheduled to undergo coronary artery bypass grafting (CABG), and being unable to undergo revascularization. There are different types of CHD, such as borderline artery lesion, acute coronary syndrome needing PCI and severe artery stenosis demanding CABG, and different stratifications of GRACE score, and these varying types mean different pathology, prognosis, and clinical risk. Thus, obtaining the association between TCM Zheng and types of coronary artery stenosis and GRACE score is crucial to advance the treatment of CHD by TCM. Although some of the recent studies focused on Zheng distributions in CHD patients based on investigations using clinical epidemiology, the association between TCM Zheng and types of coronary artery stenosis and GRACE score remains obscure. Therefore, we planned to carry out a multicenter large-sample case series study among four tertiary A hospitals in China to detect the association between TCM Zheng and types of coronary artery stenosis and GRACE score.

## 2. Objective

The study aims to determine the association between TCM Zheng and types of coronary artery stenosis and to determine the association between TCM Zheng and GRACE score.

## 3. Methods and Design

### 3.1. Study Design

This study is a multicenter, large sample, case series study. The Declaration of Helsinki and Good Clinical Practice (GCP) Guidelines are regarded as the principle of this clinical study. The protocol, informed consent, and electronic case report form (eCRF) of this study have been reviewed and approved by the Ethics Committee of Guang'anmen Hospital of the China Academy of Chinese Medical Sciences (no. 2017-058-KY-01). The participants' information and privacy will be strictly protected. Written informed consent will be obtained from each participant before the clinical information is collected. This study was registered at the Chinese Clinical Trial Registry on November 2, 2017, in both Chinese and English editions; the registration number was ChiCTR-ROC-17013221. The study design is briefly described in Figure 1.

### 3.2. Subject Recruitment

The patients had a diagnosis of coronary atherosclerosis or CHD. Normally, CHD includes borderline coronary lesion, stable angina pectoris (SAP), unstable angina (UA), non-ST-segment-elevation myocardial infraction (NSTEMI), and ST-segment-elevation myocardial infraction (STEMI); these conditions will be included in this case series study. All the patients will be enrolled from November 2017 to December 2018 at four hospitals, identified in Table 1. Three thousand eligible participants will be recruited from these four sites according to the inclusion and exclusion criteria.

### 3.3. Diagnostic Criteria

#### 3.3.1. Traditional Chinese Medicine Diagnostic Criteria of CHD Zheng

TCM Zheng of each participant will be estimated by two TCM experts referring to the “National Standard Clinical Terminology of Traditional Chinese Medical Diagnosis and Treatment–Syndromes (GB/T 16751.2-1997)” and “Traditional Chinese Medicine Syndrome Differentiation Criteria of Coronary Heart Disease” [6]. These two diagnostic criteria involve all the simple Zheng. Permutations and combinations of these simple Zheng are flexible and could encompass all the complex clinical settings. The interrater reliability of diagnosing TCM Zheng will be evaluated using the kappa statistic.

#### 3.3.2. Diagnostic Criteria of CHD

The diagnostic criteria of different types of CHD will refer to the “Guideline for the Diagnosis and Management of Patients with Stable Ischemic Heart Disease” [7] (2012 edition), the “Guideline for the Management of Patients with Non-ST-Elevation Acute Coronary Syndromes” [8] (2014 edition), and the “Guideline for the Management of ST-Elevation Myocardial Infarction” [9] (2013 edition). To establish whether patients with CHD undergo revascularization (PCI or CABG) and whether patients are unable to undergo revascularization due to contraindications, we will refer to “Guidelines on Myocardial Revascularization” [10] (2011 edition). Specifically, we list the indications for revascularization of stable coronary artery disease (SCAD) patients and recommendations for the type of revascularization of SCAD patients in Tables 2 and 3, respectively.

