## 6. Discussion

CHD is usually caused by atherosclerosis, which leads to coronary artery stenosis and myocardial ischemia. The treatment strategies for CHD include mainly drugs, PCI, and CABG. It is notable that different degree of coronary artery stenosis may bring about different clinical manifestations and outcomes. In general, patients with atherosclerosis do not have symptoms of chest pain; patients with borderline coronary lesion could manifest as stable angina; patients scheduled to undergo PCI or CABG or those unable to undergo revascularization have similar symptoms including acute coronary syndrome. Studies have indicated that some kinds of TCM Zheng, such as Qi deficiency, Yin deficiency, Yang deficiency, blood stasis, phlegm, and Qi stagnation, may be found in patients with CHD [13]. Within the framework of TCM theory, different TCM Zheng has different clinical manifestations. For instance, the CHD patient with Qi deficiency could present with chest distress, shortness of breath, lassitude, spontaneous sweating, pale tongue with white coating, and weak pulse. In addition, the CHD patient with blood stasis could manifest symptoms such as a steady stabbing pain in the chest, dark complexion, cyanotic lips and nails, scaly skin, subcutaneous ecchymosis, dark and purple tongue with ecchymosis or spots, thread, and rough or knotted and intermittent pulse. Coronary artery stenosis involves several pathophysiological aspects such as endothelial injury, lipid accumulation, intraplaque hemorrhage, platelet aggregation, and thrombogenesis, which, from the perspective of TCM Zheng, could be prevented; blood stasis and phlegm could be addressed within the framework of TCM theory [14]. Previous cross-sectional studies have often analyzed the relationship between TCM Zheng and CHD, and the inclusion criteria usually used computed tomography angiography to diagnose CHD [15]. However, in this study, we focus on CHD patients who are diagnosed by the golden standard of CAG. We are expanding the population of participants to include not only CHD patients with more than 50% coronary stenosis but also patients with simple atherosclerosis and those with 30%-50% coronary stenosis [16]. In recent years, relevant studies have found that some patients with ACS are diagnosed with normal arteries, which may result from microvascular disease and endothelial dysfunction [17]. Therefore, we hope to see if differences among varying degrees of coronary artery stenosis can be identified in TCM Zheng, which may help indicate if TCM Zheng could identify risk factors for the progression of coronary artery stenosis. The possible association between TCM Zheng and coronary artery stenosis is shown in Figure 2. Among the studies assessing TCM Zheng in CHD, we are the first to assess the GRACE score of participants, which may predict long-term cardiovascular endpoint events [18] and identify those associated with different TCM Zheng.

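### The fifth stenosis type is set apart by contraindications to revascularization rather than by a stated stenosis measure, so its Zheng contrast should not be read as a difference in degree of stenosis

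*Protocol article*

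**What the plan says.** The Introduction of the protocol article states the classification: "Based on the degree of stenosis and treatment options, coronary stenosis can be divided into 5 types". The first two types have stenosis ranges: "atherosclerosis with less than 30% stenosis, borderline coronary lesion with 30% to 70% stenosis". The third is planned PCI. The last two are "scheduled to undergo coronary artery bypass grafting (CABG), and being unable to undergo revascularization". No stenosis range is given for types 3 to 5.

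Section 3.3.2 says how the revascularization categories are established. For the fifth, the sites decide "whether patients are unable to undergo revascularization due to contraindications", by reference to a revascularization guideline. Tables 2 and 3 tie the indication for revascularization, and the choice between PCI and CABG, mainly to lesion extent in stable disease. Neither table has a criterion for type 5.

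Section 2 gives the first objective: "The study aims to determine the association between TCM Zheng and types of coronary artery stenosis". The Discussion states the intended reading: "we hope to see if differences among varying degrees of coronary artery stenosis can be identified in TCM Zheng". Section 3.6 lists past medical history, the angiography result and Zheng among the items collected.

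**The concern.** A contraindication is a reason against a procedure. Two patients with the same angiogram can fall into different types, one into type 3 or 4 and the other into type 5, because only one of them has a contraindication. If that reason is a comorbid condition, it may also produce the signs from which Zheng is diagnosed. The Discussion's own example shows the route: "the CHD patient with Qi deficiency could present with chest distress, shortness of breath, lassitude, spontaneous sweating". Breathlessness and fatigue are not specific to coronary narrowing.

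A deficiency Zheng could therefore be more frequent in type 5 than in types 3 and 4 when stenosis has no relation to Zheng at all. Read as the Discussion proposes, that excess would count as evidence on degree of stenosis. In addition, patients with a contraindication are taken out of the groups that their lesions would otherwise suggest, so types 3 and 4 contain only patients judged fit for a procedure.

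**Working it through.** **Step 1: what defines each type.**

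| Type | Defined by | Stenosis range given |
|---|---|---|
| 1 Atherosclerosis | stenosis | under 30% |
| 2 Borderline lesion | stenosis | 30% to 70% |
| 3 Planned PCI | procedure; Tables 2 and 3 link it mainly to the lesion (stable disease) | none |
| 4 Planned CABG | as type 3 | none |
| 5 Revascularization not possible | contraindication (section 3.3.2) | none |

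Types 3 and 4 also rest on treatment, but the article links them to lesion extent. It gives no such link to separate type 5 from them. Symptoms do not supply one either, since the Discussion says that "patients scheduled to undergo PCI or CABG or those unable to undergo revascularization have similar symptoms including acute coronary syndrome".

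**Step 2: what the plan's figures allow.** The article gives no share of patients in type 5, no Zheng frequency, no alpha and no effect size for this comparison. Its only calculated figure is the total: 100 × 25 × 1.15 = 2,875, which it writes as about 3,000. The point does not depend on that figure; it is used below only to size the groups.

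**Step 3: illustration.** Every input here is an assumption except the total of 3,000.
- Types 3 and 4 together hold half of the patients: 0.50 × 3,000 = 1,500. Type 5 holds 5% or 10%: 150 or 300.
- A comorbidity is present in 30% of types 3 and 4, and in 50%, 80% or 100% of type 5.
- Zheng depends on the comorbidity only, with frequency *a* when it is present and *b* when it is absent. Stenosis has no effect.

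Expected Zheng frequency in a group with comorbidity prevalence *c*: p = c·a + (1 − c)·b.

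Rejection probability of an unadjusted two-sided 5% test: Φ[(d − 1.96·se0)/se1], where d is the difference in frequency, se0 the pooled standard error and se1 the unpooled one.

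Worked case, with a = 0.60, b = 0.40, c = 0.80 in type 5 and n = 150:
- p5 = 0.8 × 0.60 + 0.2 × 0.40 = 0.56
- p34 = 0.3 × 0.60 + 0.7 × 0.40 = 0.46
- odds ratio = (0.56/0.44)/(0.46/0.54) = 1.49
- d = 0.10, se0 = 0.0427, se1 = 0.0425
- Φ[(0.10 − 1.96 × 0.0427)/0.0425] = 0.65

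| a / b | c in type 5 | p5 | p34 | Odds ratio | Rejection, n = 150 | Rejection, n = 300 |
|---|---|---|---|---|---|---|
| 0.5 / 0.4 | 0.5 | 0.45 | 0.43 | 1.08 | 0.07 | 0.09 |
| 0.5 / 0.4 | 0.8 | 0.48 | 0.43 | 1.22 | 0.22 | 0.36 |
| 0.5 / 0.4 | 1.0 | 0.50 | 0.43 | 1.33 | 0.38 | 0.61 |
| 0.6 / 0.4 | 0.5 | 0.50 | 0.46 | 1.17 | 0.15 | 0.25 |
| 0.6 / 0.4 | 0.8 | 0.56 | 0.46 | 1.49 | 0.65 | 0.89 |
| 0.6 / 0.4 | 1.0 | 0.60 | 0.46 | 1.76 | 0.91 | 0.99 |
| 0.6 / 0.3 | 0.5 | 0.45 | 0.39 | 1.28 | 0.30 | 0.49 |
| 0.6 / 0.3 | 0.8 | 0.54 | 0.39 | 1.84 | 0.94 | >0.99 |
| 0.6 / 0.3 | 1.0 | 0.60 | 0.39 | 2.35 | >0.99 | >0.99 |

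The nominal rate is 0.05. With the weakest inputs the inflation is slight, and with the strongest it is nearly complete. The table shows that a modest non-coronary gap would be detectable at this sample size. It does not show that such a gap exists.

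**The case against.** The mixed basis is open: the Introduction names treatment options alongside degree of stenosis, and the objective speaks of types, not degrees. Describing Zheng by clinical category, including patients who cannot be revascularized, is a legitimate aim for a case series. This stands, and it is why the classification itself can stay. It does not rescue the Discussion's sentence, which turns the comparison into one of degrees.

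A reader might infer that type 5 is simply a comorbidity indicator placed at the severe end of a stenosis scale. The documents do not support that. They never order the five types, and they do not say which contraindications count, so some may be anatomical. The exclusions in section 3.4.2 (among them eGFR below 30, cirrhosis, malignancy, acute stroke and respiratory failure) and the age limit of 80 in section 3.4.1 also remove much of the comorbidity on which the mechanism relies. They reduce the problem without settling it, because whatever contraindications remain still define the group.

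The article states no unadjusted test of type 5 against types 3 and 4, and adjustment may be planned in a document not shown. Missing adjustment is therefore not the point. Adjustment would in any case not turn a group defined by contraindication into a measure of stenosis.

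**Conclusion.** The point holds as one of definition and interpretation. Type 5 carries no stenosis measure that distinguishes it from types 3 and 4, and the Discussion means to read the comparison as one of degree of stenosis. Misattribution is possible to the extent that the remaining contraindications are non-anatomical and affect the signs from which Zheng is read. Its size is unknown. The range in the working rests on assumed group sizes, comorbidity prevalences and Zheng frequencies, and it should not be quoted as an estimate of the bias or as a prediction that a false association will be reported. The change is worth making because it is cheap and concerns one of the five levels of the variable in the first objective.

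**What to change.** - Keep the five types, and describe them as a clinical and treatment classification.
- Base any conclusion about degree of stenosis on a severity variable derived from the angiography result that section 3.6 already collects, for example maximum percent stenosis and number of diseased vessels. Define it in the same way for every patient, including those in type 5.
- Carry contraindication to revascularization (yes/no), which section 3.3.2 already has established, as a separate variable.
- Report contraindicated patients as a subgroup, compared with other patients of similar angiographic severity, and do not call that contrast a degree of stenosis. Reword the Discussion sentence to match.

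Moving type 5 patients into type 3 or 4 on their angiogram would not work. Those types are defined by the planned procedure, four of the nine lesion patterns in Table 3 carry Class I for both PCI and CABG, and Tables 2 and 3 cover stable disease only, whereas section 3.2 also enrols acute coronary syndromes.

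Cost: one derived variable, one more analysis table, and an imprecise comparison for what may be a small subgroup. Patient care does not change.

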### 3.4. Inclusion and Exclusion Criteria

#### 3.4.1. Inclusion Criteria

Inclusion criteria include the following:Patients with coronary atherosclerosis or with CHD.Planned coronary angiography (CAG).Participant aged from 18 to 80 years.Participants who voluntarily signed the informed consent.

#### 3.4.2. Exclusion Criteria

Exclusion criteria include the following:Participants with acute infection, trauma, burns, and surgical history in the previous week.Participants who have already received PCI or CABG or have received other vascular (including cardiocerebral vascular and peripheral vascular) interventional treatments.Uncontrolled hypertension (occasional resting blood pressure higher than 160/100 mmHg in one week, under drug control), severe ventricular arrhythmia, and III-degree atrioventricular block.Other heart diseases such as rheumatic heart disease, pulmonary heart disease, hyperthyroidism heart disease, dilated cardiomyopathy, hypertrophic cardiomyopathy, severe valvular disease, myocarditis, and pericarditis.Participants with aortic dissection, aortic aneurysms, pulmonary embolism, and severe myocardial bridge.Participants with acute exacerbation of chronic obstructive pulmonary disease and respiratory failure.Participants with liver dysfunction and alanine aminotransferase (ALT)>3 times the normal value or combined with cirrhosis; with kidney dysfunction and estimated glomerular filtration rate (eGFR)<30 mL/min/1.73 m^2^.Participants with hematopoietic system disease, malignant tumor, autoimmune disorders, and infectious disease (tuberculosis, viral hepatitis, syphilis, and acquired immune deficiency syndrome).Participants with acute cerebral stroke and severe complications of diabetes (diabetic foot, diabetic ketoacidosis).Participants with organ transplantation.Participants with psychosis or dysgnosia.Pregnant or lactating women.

### 3.5. Sample Size

In the multifactor statistical analysis, the sample size is usually 5-10 times of the number of variables [11]. In actual use, there have been some false-positive and false-negative errors. In addition, to improve accuracy, the overall sample size is usually designed to be 20-30 times of the number of variables (items in the scale). This study contains approximately 100 variables. Considering a nonresponse rate of at least 15%, the final overall sample design is estimated as 100 × 25 × (1 + 15%) ≈ 3000 cases, with a 95% confidence interval and 2% relative error.

### 3.6. Observational Content

The observational content would include (1) demographics: age, sex, home address, education, height, and weight; (2) life style: smoking history and alcohol consumption history; (3) past medical history; (4) medication history; (5) TCM symptoms: the main complaint, feeling of coldness or fever, perspiration, discomfort in parts of body from head to toe, appetite, quality of sleep, stool, urine, the condition of the tongue and pulse, and so on; (6) TCM Zheng; (7) clinical diagnosis; (8) CAG result; and (9) GRACE score.

## 4. Quality Control

Quality control is crucial in a multicenter study to ensure the accuracy and authenticity. Quality control measures chiefly include organization structure, investigator training, standard operating procedures (SOP), and supervision and internal inspection.

### 4.1. Organization Structure

The multicenter clinical study will be directed and coordinated by the project leader. In addition, the principle investigator (PI) of every site will be responsible for the assignment of work and the quality control of this study. Meanwhile, a study monitor, who is not directly involved in participant enrollment and information collection, will be authorized by the project leader to supervise this study.

### 4.2. Investigators Training

Before starting the clinical study, all the investigators should participate in strict and systematic training to ensure the accuracy of participant information. We will carry out intensive training or online video training for all investigators; the training contents include (1) aim, method and SOP; (2) the standardized process for completing the clinical questionnaire; (3) eCRF usage; and (4) information and data management.

